### Aims of the study

The primary aim of the study is to evaluate whether graduated elastic compression stockings compared to inactive (placebo) stockings, worn daily for 2 years after DVT is diagnosed, decrease the incidence of PTS.

Secondary aims are 1) to evaluate whether active compared with inactive stockings reduce the severity of PTS, 2) to compare mean quality of life (QoL) scores during follow-up in the active intervention vs. control groups, 3) to describe the rates of recurrent DVT, death from VTE, venous ulcers, and major bleeding during the 2-year follow-up in the active intervention vs. control groups, 4) to evaluate the cost-effectiveness of ECS for the prevention of PTS, and 5) to determine whether markers of inflammation, D-dimer and thrombophilia influence the development and severity of PTS (Bio-SOX biomarker substudy).

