** *Enrollment visit* **
• The nurse completes the baseline form (inclusion/exclusion criteria, demographic and clinical variables, results of objective tests for DVT), PTS scale and pain scale
• The patient self-completes the QOL form
• The nurse performs the leg measurements to size the stockings
• The nurse teaches patients how to apply (using a plastic leg model) and care for stockings (handling, washing), and reinforces the importance of daily use
• Study stockings are supplied to the patient (within a few days after enrollment)
• A venous blood sample is taken for markers of inflammation

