**1-year visit**
• Same as 6-month visit except no blood sampling
• A venous ultrasound is performed to assess reflux

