### Sample size and power calculations

We hypothesized that event rates (i.e. PTS at 2 years) will be 30% in the inactive stocking vs. 20% in the active stocking group, i.e. a risk reduction of 33%. Our baseline event rate and effect size for the stocking group were based on a systematic review of available published data [68]. The total sample size required to detect this difference in event rates with a two-tailed α of 0.05 and 80% power is 600 [69]. We increased our sample size to 800 to take into account a projected 25% loss-to-follow up by 2 years.

For the biomarker analyses, our sample size provides > 80% power to detect ORs of 0.5 or lower, or 2.0 or higher. Larger alternatives will be associated with increased power. With regard to inflammatory markers, the analysis will be largely exploratory, as this study will be among the first to provide prospective data on levels of markers of inflammation in patients with DVT and PTS. However, the study design provides power of at least 80% to detect differences on the order of 1/3 of a standard deviation or larger between initial values of inflammatory markers in the two allocation groups.

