For the secondary outcomes valvular reflux, recurrent VTE, death from VTE, venous ulcer, major bleeding, and severity of PTS, rates in the two intervention groups will be described, and between-group differences explored in similar regression procedures. For differences in mean quality of life scores between intervention groups, analysis of variance incorporating treatment and center will be used. A difference of 4–5 points between groups is considered to be clinically meaningful. Analysis of covariance with adjustment for age, sex and comorbidity will also be used to compare quality of life between groups. For the biomarker variables, univariate analysis will be used to determine the strength of association between each biomarker variable and the occurrence of PTS. For genetic markers, heterozygotes and homozygotes will be analyzed together, given the rarity of homozygotes. IgG, IgM and lupus anticoagulant results will be dichotomized as normal or abnormal. Factor VIII, D-dimer and markers of inflammation will be analyzed both as continuous data and as proportion of values exceeding the upper 90^th ^percentile. For binary and nominal data, the appropriate chi-square tests will be used to examine the respective crude associations, and for continuous variables, the unpaired 2-tailed t-test. To examine adjusted associations, multiple logistic regression analyses will be performed in which the dependent variable is the presence of PTS. The independent variables to be tested are markers of thrombophilia, D-dimer, and levels of CRP, IL-6, IL-8 and MCP-1. Other variables of interest (for interaction and/or confounding) are age, sex, ethnicity, comorbid illness, allocation to active ECS, type and duration of heparin and warfarin use, type of DVT (unprovoked vs. secondary; anatomic extent of DVT), and recurrent DVT during follow-up. The analyses will aim to (1) identify the strength of the association between relevant biomarkers, other relevant explanatory variables and PTS; and (2) explore relevant interactions. Similarly, multiple linear regression will be performed in which the dependent variable is the severity of PTS, as measured by the Villalta scale.

An interim analysis for efficacy will be performed when half of the subjects have completed 2 years of follow-up. The analysis plans call for a Lan-DeMets alpha spending approach with an O'Brien Fleming boundary [70].

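### Neither stated quality-of-life model adjusts for the enrollment QoL score, which the trial already collects, and this costs precision

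*Protocol article*

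**What the plan says.** Under Aims of the study, the second secondary aim is "to compare mean quality of life (QoL) scores during follow-up in the active intervention vs. control groups". The instruments are the SF-36 and the VEINES-QOL/Sym.

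Under Statistical analysis, two models are named. The first: "For differences in mean quality of life scores between intervention groups, analysis of variance incorporating treatment and center will be used". The second: "Analysis of covariance with adjustment for age, sex and comorbidity will also be used to compare quality of life between groups". The same section gives a yardstick for the result: "A difference of 4–5 points between groups is considered to be clinically meaningful".

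Table 1 shows when the scores are collected. At the enrollment visit, "The patient self-completes the QOL form". The same item stands at 1 month, 6 months and 2 years. The 1-year and 18-month visits inherit it through "Same as 6-month visit except no blood sampling". That makes one enrollment score and five follow-up scores per scale. Study stockings reach the patient within a few days after enrollment, so the enrollment score precedes their use.

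**The concern.** The article lists the terms of both QoL models, and the enrollment value of the outcome is in neither. A patient's earlier score on the same scale usually carries information about the later score. When it is left out, that between-patient variation stays in the error term.

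The comparison remains fair, because randomization balances enrollment QoL in expectation. At stake is the width of the confidence interval around a difference of 4 to 5 points, the size the protocol itself calls meaningful. A wider interval makes it harder to show such a difference or to exclude one. An analysis plan that followed the article's wording would carry the omission forward.

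**Working it through.** **Inputs from the article**

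- QoL models: treatment and center; and age, sex and comorbidity (Statistical analysis).
- QoL assessments: enrollment plus 1, 6, 12, 18 and 24 months (Table 1).
- Meaningful difference: 4–5 points.
- Sample size: 600, raised to 800 for a projected 25% loss by 2 years.
- No standard deviation, correlation or power is given for QoL.

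**The plan's own figure**

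The sample size is set for the primary outcome: "event rates (i.e. PTS at 2 years) will be 30% in the inactive stocking vs. 20% in the active stocking group", and "The total sample size required to detect this difference in event rates with a two-tailed α of 0.05 and 80% power is 600". With z-values 1.960 and 0.842 and mean rate 0.25, the pooled formula per arm is

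n = [1.960·√(2·0.25·0.75) + 0.842·√(0.3·0.7 + 0.2·0.8)]² / 0.10² ≈ 293.2, so 294 per arm and 588 in total.

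This is within 3% of 600, and 600/(1 − 0.25) = 800. The figure reproduces. Below, 600 (300 per arm) serves only as the number of patients with 2-year data; it was not derived for QoL.

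**Gain for a single follow-up visit**

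Let ρ be the correlation of the enrollment score with the follow-up score (assumed). Adjusting for the enrollment score multiplies the residual variance by 1 − ρ². The equivalent unadjusted sample is 600/(1 − ρ²).

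| ρ (assumed) | Variance factor | Cut in variance | Equivalent of 600 |
|---|---|---|---|
| 0.3 | 0.91 | 9% | 659 |
| 0.4 | 0.84 | 16% | 714 |
| 0.5 | 0.75 | 25% | 800 |
| 0.6 | 0.64 | 36% | 938 |

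**Gain if the five follow-up scores are averaged**

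Let r be the correlation between any two follow-up visits (assumed equal for all pairs), with equal variances. Relative to one visit, the variance of the five-visit mean is (1 + 4r)/5. With baseline adjustment it is (1 + 4r)/5 − ρ². At r = 0.5 the unadjusted value is 3/5 = 0.60.

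- ρ = 0.3: (0.60 − 0.09)/0.60 = 0.51/0.60 = 0.85, a cut of 15%.
- ρ = 0.5: (0.60 − 0.25)/0.60 = 0.35/0.60 = 0.58, a cut of 42%.

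**What this could mean for power**

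This uses 300 per arm, a true difference of 4 points, two-sided α of 0.05 and a single visit. The standard deviations are assumptions.

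| SD (assumed) | Unadjusted | Adjusted, ρ = 0.3 | Adjusted, ρ = 0.5 |
|---|---|---|---|
| 15 | 90.4% | 92.8% | 96.5% |
| 20 | 68.8% | 72.8% | 80.7% |
| 25 | 50.0% | 53.8% | 61.9% |

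Check of one cell: for SD 20 the standard error is 20·√(2/300) = 1.633. Then 4/1.633 − 1.960 = 0.489, and the normal probability below 0.489 is 0.688.

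These gains are measured against the model with treatment and center. Against the model with age, sex and comorbidity the extra gain may be smaller, because those covariates may already explain part of what the enrollment score explains.

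**The case against.** Several points on the other side are sound.

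- **No bias.** With complete data the analysis of variance is a valid comparison of randomized groups. Nothing in the article is wrong or contradictory here. This stands, and it limits the point to efficiency on a secondary outcome.
- **The size is not known.** Without a standard deviation or a correlation, the article cannot show that the QoL aim is underpowered. At an assumed SD of 15, power for 4 points is already about 90%. This stands too.
- **The correlation may be low.** Eligibility requires a DVT diagnosed within the last 10 days, so the enrollment score reflects acute illness and may predict later QoL only weakly. At ρ = 0.3 a single-visit comparison gains 9% of variance, which is about 5% of the standard error (1 − √0.91).
- **An article condenses.** Visit structure and missing-data handling may be left to a fuller plan. That does not cover the covariates: the article lists them for both models and omits this one. Its mention of adjusting for pertinent baseline variables concerns the primary outcome and differences between groups, not QoL.

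A reader might go further and infer that the five follow-up scores are ignored, or that QoL is compared visit by visit among patients who completed that visit. The text does not support either. It names no visit, the aim speaks of mean scores during follow-up, which can mean an average over visits, and intention-to-treat is stated for all outcomes. The projected 25% loss is a figure for 2 years, not for each visit.

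**Conclusion.** The point holds as one of precision. Both QoL models are given with their terms, and both leave out an enrollment score that the trial collects. Adjustment would reduce variance on either reading of the aim, provided the scores correlate at all:

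- by 9% to 36% for a single visit, at an assumed baseline correlation of 0.3 to 0.6;
- by about 15% to 42% for a five-visit average, at an assumed between-visit correlation of 0.5 and a baseline correlation of 0.3 to 0.5.

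The low end is plausible here. The primary outcome is untouched, and no bias follows when data are complete. The change should be made because it is simple and uses data already in hand; the trial's conclusions do not depend on it.

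**What to change.** State that each QoL comparison includes the enrollment score of the same scale as a covariate, together with treatment and center, and keep age, sex and comorbidity as additional baseline covariates.

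A suitable way to do this is a repeated-measures mixed model over the five follow-up visits, with treatment, visit, their interaction, center and the enrollment score. Report the average follow-up difference and the 2-year difference, each with a 95% confidence interval. The average fits the stated aim directly, and the model makes explicit how the five scores are used. A simpler analysis of covariance that includes the enrollment score would also answer the main point.

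The cost is a change of wording in the analysis plan, made before treatment codes are broken. No new data, visits or patients are needed.

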### Potential role of inflammation, d-Dimer and thrombophilia in the post-thrombotic syndrome

While the pathophysiology of PTS is incompletely understood, it is likely that the acute thrombus itself, associated mediators of inflammation, and the process of vein recanalization in the weeks following DVT induce damage to venous valves, leading to valvular incompetence (reflux). Valvular incompetence and/or persistent venous obstruction by thrombus cause venous hypertension, which promotes capillary leakage of plasma proteins, erythrocytes and leukocytes and the development of venous ectasia and varicosities. The result is edema, tissue hypoxia, and ultimately, in some cases, skin ulceration [11-14].

Inflammation and thrombosis are closely interrelated [15-17]. It has been appreciated over the last few years that arterial atherothrombosis is, at least in part, an inflammatory disease, and that elevations in markers of inflammation, such as C-reactive protein (CRP), increase the risk of future clinical cardiovascular events [18]. Clinically, patients with DVT exhibit cardinal signs of inflammation such as redness, warmth, swelling, pain and fever. Several clinical studies have examined the association between levels of inflammatory markers and venous thrombosis, and found that a two- to six-fold increase in the risk of DVT associated with elevations in plasma levels of CRP, interleukin (IL)-6, IL-8, monocyte chemotactic protein (MCP)-1 or tumor necrosis factor (TNF)-alpha [19]. A recent paper showed that CRP is elevated in patients with acute DVT (median 37.5 mg/L) compared with controls (5.0 pg/L), and that levels decline during the first 5 days of DVT treatment. Similar trends were noted for IL-6 [20], leading the authors to conclude that the thrombotic process produces a systemic inflammatory response and to speculate whether the observed decrease in levels was partly caused by treatment with heparin, which is known to have anti-inflammatory properties distinct from its anticoagulant properties [21]. Whether levels of markers of inflammation are predictive of PTS has not previously been examined.

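### The covariates listed for the biomarker models omit the enrollment PTS-scale and pain scores, so an enrollment inflammatory marker that only tracks leg status at entry could look like a predictor of PTS

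*Protocol article*

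**What the plan says.** The Statistical analysis section of the protocol article describes multiple logistic regression with PTS as the outcome. It names the markers: "The independent variables to be tested are markers of thrombophilia, D-dimer, and levels of CRP, IL-6, IL-8 and MCP-1". It then names the adjustment variables: "Other variables of interest (for interaction and/or confounding) are age, sex, ethnicity, comorbid illness, allocation to active ECS", followed by type and duration of heparin and warfarin, and "type of DVT (unprovoked vs. secondary; anatomic extent of DVT), and recurrent DVT during follow-up". The severity model is set up in the same way: "Similarly, multiple linear regression will be performed in which the dependent variable is the severity of PTS, as measured by the Villalta scale".

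The Enrollment visit entry in Table 1 has the nurse record "demographic and clinical variables, results of objective tests for DVT), PTS scale and pain scale". A blood sample for inflammatory markers is drawn at that visit. Further inflammatory samples are drawn at 1 and 6 months, the genetic thrombophilia sample at 1 month, and D-dimer and the coagulation assays at 6 months.

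The Background section on inflammation, D-dimer and thrombophilia states: "Clinically, patients with DVT exhibit cardinal signs of inflammation such as redness, warmth, swelling, pain and fever". The outcome section diagnoses PTS from typical pain and swelling that last at least one month and are present at least six months after the DVT. It grades severity on the Villalta scale.

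**The concern.** Biomarker levels are not randomized, so only covariate adjustment protects these associations from confounding. The article itself supplies a possible route: it ties swelling and pain to inflammation in acute DVT, and later defines PTS by pain and swelling. A patient with a worse leg at entry may have both a higher enrollment CRP or IL-6 and more leg symptoms at two years, without the marker adding any information of its own. The gap is most direct in the severity regression, where a PTS scale has been scored at entry but is not among the covariates.

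The Abstract and Discussion speak of a predictive role for biomarkers, and the Discussion looks ahead to therapies aimed at candidate biomarkers. A reader will want to know whether a marker says more than the nurse has already scored. Models built only from the listed covariates cannot answer that.

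**Working it through.** **The plan's own numbers.** For 30% versus 20%, two-sided alpha 0.05 and 80% power, the pooled two-proportion formula gives 294 per arm, 588 in total. This is close to the stated 600; 300 per arm gives 80.9% power. Then 600/(1 − 0.25) = 800. The point disputes none of these figures. They supply n = 600 evaluable patients and an average PTS risk of (30% + 20%)/2 = 25%.

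**Assumed inputs, not in the document.** Let r1 be the correlation of the enrollment marker with the enrollment score, and r2 the correlation of that score with later Villalta severity. Suppose the marker has no effect of its own.

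**Severity model.** The induced marker–severity correlation is ρ = r1 × r2. The chance of a two-sided p<0.05 by Fisher's z is Φ(d − 1.96) + Φ(−d − 1.96), where d = atanh(ρ) × √(600 − 3) and √597 = 24.43.

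| r1 / r2 | ρ | d | chance of p<0.05 |
|---|---|---|---|
| 0.1 / 0.1 | 0.01 | 0.24 | 0.043 + 0.014 = 0.057 |
| 0.2 / 0.2 | 0.04 | 0.98 | 0.163 + 0.002 = 0.165 |
| 0.3 / 0.3 | 0.09 | 2.20 | 0.60 |
| 0.3 / 0.4 | 0.12 | 2.95 | 0.84 |
| 0.4 / 0.5 | 0.20 | 4.95 | >0.99 |

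With the score in the model, the marker's expected coefficient is zero under these assumptions.

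**Binary PTS model.** This was checked by logistic simulation: 400 runs per setting, n = 600, PTS about 25%, a marker with no effect of its own, and an assumed odds ratio (OR) per SD of the enrollment score.

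| correlation r, OR per SD of score | apparent OR per SD of marker, score omitted | p<0.05, score omitted | p<0.05, score included |
|---|---|---|---|
| 0, 2.0 | 0.99 | 6% | 6% |
| 0.1, 1.5 | 1.04 | 4% | 4% |
| 0.3, 2.0 | 1.20 | 48% | 7% |
| 0.5, 2.5 | 1.52 | 99% | 5% |

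Over all settings with r from 0.1 to 0.5 and OR from 1.5 to 2.5, rejection ran from about 4% to 99% without the score and about 4% to 8% with it. The Monte Carlo standard error near 5% is √(0.05 × 0.95/400) = 1.1 percentage points.

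**Precision.** The score alone explains r2² of the severity variance: 9%, 16% and 25% for r2 = 0.3, 0.4 and 0.5. The gain for the marker's own coefficient is smaller, because marker and score are correlated. Its variance changes by the factor (1 − r2²)/[(1 − r1²)(1 − ρ²)]:

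- 0.3/0.3: 0.91/(0.91 × 0.9919) = 1.01
- 0.3/0.4: 0.84/(0.91 × 0.9856) = 0.94
- 0.4/0.5: 0.75/(0.84 × 0.96) = 0.93

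The main reason for the change is therefore interpretation, not precision.

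**The case against.** - **The list need not be closed.** It is introduced as variables of interest, the aims that follow mention further explanatory variables without naming them, and a condensed article may leave the final covariates to an analysis plan. This stands in part. Still, the list is detailed, and it names an event during follow-up (recurrent DVT) while leaving out a leg score collected at entry.
- **The score may be a mediator.** Eligibility requires a DVT diagnosed within the last 10 days, so the enrollment score is taken in the acute phase and may itself result from inflammation. Adjusting for it could remove part of a real effect. This stands, and it rules out relying on the adjusted estimate alone.
- **The aims do not promise incremental prediction.** The secondary aim asks whether markers influence PTS, and the analysis section speaks of strength of association. A marker that tracks leg status and precedes PTS still predicts it in the plain sense. This stands; the two questions need separate estimates.
- **The scope is narrow.** Inherited genotypes cannot reflect leg symptoms, and D-dimer and the coagulation assays are drawn at 6 months. The sample size section calls the inflammatory-marker analysis largely exploratory. All of this stands.
- **Pre-existing disease is partly handled.** Only first DVT is eligible, comorbid illness is a covariate, and acute symptoms do not in themselves meet the PTS definition. This stands, although other chronic venous disease is not an exclusion, and entry symptoms need only predict later ones to confound.
- **Table 1 does not name the scale.** It says "PTS scale and pain scale", so calling the entry score the baseline value of the Villalta outcome goes slightly beyond the text.

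**Conclusion.** The point holds as a limited one. Two relevant scores are collected alongside the first inflammatory sample and are missing from the stated covariates of both biomarker models. An enrollment inflammatory marker could then look predictive only because it tracks leg status at entry. The size is open: from near the nominal 5% when the correlations are weak to about 60–99% for r1/r2 of 0.3/0.3 to 0.4/0.5. These figures assume n = 600, no effect of the marker itself, and correlations that the article does not give.

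A reader might infer that a spurious marker will be reported as a predictor. The documents do not support that: nothing in them shows that the markers correlate with the entry score or that the score predicts PTS. Nor do they support treating the adjusted estimate as the only valid one, given the possible mediation. The genetic markers and the primary comparison of stockings are not touched. The point is minor and worth making because it is cheap to settle.

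**What to change.** In the Statistical analysis section, state that for enrollment inflammatory markers the logistic model for PTS and the linear model for Villalta severity will each be fitted with and without the enrollment PTS-scale and pain scores, and that both results will be reported.

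State how each is read. The model without the scores gives the total association. The model with them gives prediction beyond leg status at entry, and added prognostic value is claimed only from it. Add that the acute score may lie on the pathway from inflammation to PTS, so attenuation alone does not rule out a real inflammatory effect.

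The cost is one or two degrees of freedom and a second column of estimates. Both scores are already collected, and neither the sample size nor the primary analysis changes.

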### Risk factors for the development of PTS

While hereditary and acquired risk factors that predispose to the development of VTE are widely known [6], factors that influence the development of PTS after DVT have not been well elucidated. The only clearly identified clinical risk factor for PTS is recurrent, ipsilateral DVT [7,8]. The site (proximal vs. distal), size and occlusiveness of the initial DVT and the intensity (i.e. target INR) of long term anticoagulation for DVT do not appear to reliably predict PTS [1,7-10]. It is not clear why some patients develop PTS while others recover from their DVT. As a result, physicians are unable to provide their DVT patients with reliable, individualized prognostic information.

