D-dimer is a degradation product of cross-linked fibrin that reflects fibrinolysis and is an indirect marker of coagulation activation. Recent work performed by our group and by others suggests that D-dimer levels appear to be a significant predictor of first VTE [22] and of recurrent VTE [23-28], whether measured during or after anticoagulation. Independent of VTE recurrence, persistent coagulation activation, as reflected by elevated D-dimer levels, may also predict a higher risk of developing PTS after DVT [29].

Thrombophilia refers to an inherited or acquired predisposition to VTE. Over 10% of the general population is affected by one or more identifiable inherited thrombophilias which have been shown to underlie at least 1/3 of cases of VTE [30]. The most common inherited thrombophilias are the single nucleotide polymorphisms Factor V Leiden, which renders coagulation factor V resistant to the anticoagulant effects of activated protein C [31], and Prothrombin G20210A, which leads to elevated plasma prothrombin levels [32,33]. Recent studies have also established that elevation of Factor VIII level is an inherited risk factor both for first and for recurrent VTE [34-36], independent of age, sex, Factor V Leiden, Prothrombin G20210A or markers of acute phase activation such as CRP [35,37,38].

While results of a few studies to date suggest that thrombophilia does not increase the risk of developing PTS [7,8,10], not all thrombophilias have been examined and interactions among disorders have not been studied. Further investigation of the potential link between thrombophilia and PTS is warranted.

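### The adjusted biomarker models list recurrent DVT during follow-up as a possible confounder without splitting it at the blood sample, so for D-dimer and Factor VIII a baseline-adjusted total association with PTS is not assured

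*Protocol article*

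**What the plan says.** All places are in the protocol article.

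- **Aims of the study**, fifth secondary aim: "to determine whether markers of inflammation, D-dimer and thrombophilia influence the development and severity of PTS".
- **Statistical analysis**, crude step: "univariate analysis will be used to determine the strength of association between each biomarker variable and the occurrence of PTS", by chi-square tests and t-tests.
- **Statistical analysis**, adjusted step, a multiple logistic regression for presence of PTS: "The independent variables to be tested are markers of thrombophilia, D-dimer, and levels of CRP, IL-6, IL-8 and MCP-1". A list of candidate covariates comes next and opens with "Other variables of interest (for interaction and/or confounding) are age, sex, ethnicity, comorbid illness, allocation to active ECS, type and duration of heparin and warfarin". After the kind and extent of the DVT, it ends with "and recurrent DVT during follow-up". A linear regression for Villalta severity is to be done in the same way.
- **Risk factors for the development of PTS**: "The only clearly identified clinical risk factor for PTS is recurrent, ipsilateral DVT".
- **Potential role of inflammation, d-Dimer and thrombophilia in the post-thrombotic syndrome**: "D-dimer levels appear to be a significant predictor of first VTE [22] and of recurrent VTE". The same section calls raised Factor VIII a risk factor for recurrent as well as first VTE. It also suggests that D-dimer may predict PTS by a route that does not involve recurrence.
- **Table 1**: inflammatory markers are sampled at enrollment, 1 month and 6 months, genetic thrombophilia at 1 month, and D-dimer and the coagulation-based assays at 6 months.

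**The concern.** A confounder must not be a consequence of the exposure. A recurrence after the sample cannot have caused the measured marker level. By the article's own background it may be one of the ways in which a high D-dimer or Factor VIII leads to PTS. Conditioning on it removes that route and can add bias through shared causes of recurrence and PTS.

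The covariate is defined over the whole follow-up, so it mixes two roles. For a 6-month sample, recurrence before 6 months may be a true confounder, while recurrence after 6 months may be an intermediate. The roles the plan offers, interaction and confounding, do not include the second. A routine check of whether the estimate moves on adjustment would tend to keep recurrence in the model because it attenuates the marker.

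At stake is what a Bio-SOX odds ratio means. Asking whether a marker influences PTS reads most naturally as a question about its total association. The background also names individual prognosis as the unmet need, and later recurrence is unknown when a prognosis is given.

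**Working it through.** **1. The path, from the documents.** D-dimer and Factor VIII to recurrent VTE: stated, without a size. Recurrent ipsilateral DVT to PTS: stated, without a size. Together these give marker → recurrence → PTS for those two markers. No such link to recurrence is stated for CRP, IL-6, IL-8, MCP-1 or the individual polymorphisms.

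**2. What the planned analyses deliver.**

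| Analysis | Baseline factors adjusted | Post-sample recurrence conditioned on | Estimates |
|---|---|---|---|
| Univariate tests | No | No | Crude association |
| Logistic or linear model, all listed variables | Yes | Yes | Association not explained by recurrence |
| Not named | Yes | No | Baseline-adjusted total association |

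**3. Figures taken from the plan.** The plan gives no figure for this attenuation. Its event rates supply the overall PTS risk: (30% + 20%)/2 = 25% at 1:1 allocation. The sample size built on them reproduces closely: n per arm = [1.96√(2×0.25×0.75) + 0.8416√(0.3×0.7 + 0.2×0.8)]² / 0.10² = 293.2, so 294 per arm and 588 in total, against the stated 600; 600/0.75 = 800. The plan's 90th-percentile cut gives 10% marker-positive.

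**4. Assumptions (not in the documents).** Overall recurrence 5–15%; marker–recurrence OR 2–4; recurrence–PTS OR 2–6; direct marker–PTS OR 1.0, 1.5 or 2.0.

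**5. Formula.** Let r0 and r1 be the recurrence risk in marker-negative and marker-positive patients, and p(m,r) the PTS risk for marker status m and recurrence status r under a logistic model. Then q_m = (1 − r_m)·p(m,0) + r_m·p(m,1), total OR = [q1/(1 − q1)] / [q0/(1 − q0)], and the share of the log OR lost by adjustment = 1 − ln(direct OR)/ln(total OR).

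**6. Worked example.** Recurrence 10% overall, marker–recurrence OR 3, recurrence–PTS OR 4, direct OR 1.5.
- r0 = 8.65%, r1 = 22.13% (check: 0.9×8.65 + 0.1×22.13 = 10.0).
- PTS risks: 21.13% (neither), 51.73% (recurrence only), 28.67% (marker only), 61.65% (both).
- q0 = 0.9135×0.2113 + 0.0865×0.5173 = 0.238; q1 = 0.7787×0.2867 + 0.2213×0.6165 = 0.360.
- Total OR = (0.3597/0.6403)/(0.2378/0.7622) = 1.80. The adjusted model targets 1.50. Share lost = 1 − 0.405/0.588 = 31%.

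**7. Over the whole assumed range.**

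| Direct (adjusted) OR | Total OR | Share of log OR lost |
|---|---|---|
| 1.0 | 1.03–1.59 | All |
| 1.5 | 1.54–2.24 | 7–50% |
| 2.0 | 2.05–2.86 | 4–34% |

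**8. No marker–recurrence link (OR 1).** Nothing is lost. With a direct OR of 1.5–2.0 the adjusted log OR is 0.6–12% larger than the unadjusted one, because the odds ratio is non-collapsible. Attenuation is therefore not a general property of these models.

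**The case against.** There is a fair case that this matters little.

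- **The list is of candidates.** Recurrence is named for interaction or confounding, and the final model may be fixed in an analysis plan that is not shown. This stands: the article does not commit to adjusting for it. But neither named role fits an intermediate.
- **The crude association will be reported.** This stands too. A reader might infer that a marker acting through recurrence would simply be declared unrelated to PTS; the univariate analyses do not support that. They are, however, unadjusted for age, comorbidity or DVT extent, so they do not replace a baseline-adjusted estimate.
- **A recurrence-adjusted model has a purpose.** The background suggests a D-dimer effect apart from recurrence, and such a model addresses it. This is a reason to keep that model and label it.
- **Recurrence may be a real confounder for a 6-month D-dimer.** This stands for recurrence before the sample and is a reason to split the variable by date.
- **Power is low either way.** With 600 patients, 25% PTS and no direct effect, a total OR of 1.17–1.35 would have 11–27% power at 20% marker-positive and 8–18% at 10%. Test results would often agree across models. The estimates would still answer different questions.

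Two stronger readings are tempting. One is that warfarin duration is also an intermediate. The documents never place it between a marker and PTS, and anticoagulation up to a 6-month sample may confound the measured D-dimer. The other is that all the biomarkers are pulled toward the null. The background documents the link to recurrence only for D-dimer and Factor VIII.

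**Conclusion.** The point holds for D-dimer and Factor VIII and for recurrence after the sample. Adjusting for recurrence over the whole follow-up mixes a possible confounder with a possible intermediate. If all listed variables enter, the plan yields a crude association and a recurrence-conditioned one, but no baseline-adjusted total association.

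The size cannot be derived from the documents. Under the stated assumptions the loss is 4–50% of the log OR when a direct OR of 1.5–2.0 exists, all of it when the marker acts only through recurrence, and none when the marker does not affect recurrence.

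This is a low-cost clarification confined to Bio-SOX, whose inflammatory-marker analysis the article itself calls mainly exploratory. A reader should not carry it over to the primary stocking comparison, which uses a separate model initially adjusted only for center.

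**What to change.** State that the main adjusted biomarker analysis targets the total association. For both the logistic model of PTS and the linear model of Villalta severity:

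1. Include only variables known at or before the relevant blood sample. For the 6-month assays, that includes recurrence and anticoagulation up to the sample where relevant. The DNA polymorphisms precede any recurrence, so recurrence cannot confound them at any date.
2. Exclude recurrence after the sample from this model.
3. Report a second model that adds post-sample recurrence, labelled as a secondary analysis of the association independent of recurrence. It serves the D-dimer hypothesis in the background, and its text should note possible bias from shared causes of recurrence and PTS.

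Later anticoagulation stays out of the main model only because it is not yet known at the sample, not because the documents show it to be an intermediate.

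Cost: a change of wording, splitting recurrence by its date relative to the sample, and one extra set of estimates to report. No new study procedures are needed, and the primary analysis does not change.
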